#### Secondary outcomes II: behavioral measures

##### Functional vision: reading skills

Reading skills will be measured, separately for each eye, using the standardized MNRead test [43]. This test is administered through an app on an iPad^©^ and is designed to assess reading skills in people with low vision (MNRead, French electronic version, 2016). The MNRead measures the smallest print readable by the person without making errors (e.g., misread or missing words, according to the MNRead instructions), as well as the smallest print that the person can read with maximum speed and the maximum reading speed. However, as fluent reading is necessary for this test, only children from 8 years old will perform it.

##### Selective attention processes

Visual and audiovisual selective attention will be measured with a selective-attention task, administered separately for each eye. The paradigm is a spatial cueing task of Folk et al. (1992) [44], adapted to multisensory settings and so that it is child-friendly [45, 46]. Participants search for a target diamond of a predefined color (e.g., blue) in an array of four differently colored bars and will report the bar’s orientation (i.e., horizontal or vertical) by pressing one of two large buttons. On every trial, the search array is preceded by a task-irrelevant visual distractor, appearing randomly in one of the four stimulus locations. The distractor is either of the same color as the target (e.g., blue), or of another, non-target color (e.g., red). On half of all trials the visual distractor is presented together with a spatially diffuse tone (audiovisual distractor). The target color will be counterbalanced across participants.

Two types of selective attention processes will be measured: top-down, goal-based visual attention and bottom-up, stimulus-driven multisensory attention. They will be assessed behaviorally and electrophysiologically (EEG), comparable to Folk et al. [44] and Turoman et al. [45, 46], respectively. Behaviorally, the two processes of selective attention will be measured using spatial cuing effects, i.e., the difference in speed of responding when the cue and target are in the same vs. different locations. Specifically, the strength of visual selective attention will be measured by the difference in cuing effects elicited by distractors that matched vs. mismatched the target’s color. The strength of audiovisual selective attention will be measured by the difference in cuing effects elicited by the color distractors that appeared alone vs. with the sound.

Motor control: Reaching and GRAsping at different Depths (ReGraD) Task.

Motor planning and execution deficits will be evaluated during a visually guided reach-to-grasp task at different reaching depths using reflective markers attached to the fingers and hand. The participant sits in front of a wooden box (where the pegs are initially inserted) and a cylinder (where the pegs are to be inserted). The box is mounted on a tripod that can be adjusted to the participant height and arm length. There are two equally sized pegs that are placed by the experimenter in the box differing by their color on the tip of the peg. The participant is instructed to focus on the target peg (green) and ignore the flanker peg (red). The participant needs to reach and grasp the target peg by estimating its depth and insert it in the cylinder. The board on the wooden box has 2 rows of 3 holes (right on top of each other) where the pegs can be inserted. The target and flanker pegs can be inserted in the same column, with 1 or 2 column difference, to increase depth between the pegs. There will be a total of 90 trials to complete with each eye condition (dominant eye, non-dominant eye and with both eyes):(i) No depth difference: 20 trials (5 trials with target in close-top position, 5 trials with target in further-top position, 5 trials with target in close-bottom position and 5 trials with target in further-bottom position). In this condition, the flanker does not influence stereovision perception.(ii) One level of depth difference: 20 trials (10 with the target in front (5 up and 5 bottom) and 10 (5 up and 5 bottom) with the flanker in front). In this condition, the flanker may influence stereovision perception either when it is located in front or after the target peg.(iii) Two levels of depth difference: 20 trials with two levels of depth difference (10 with the target in front (5 up and 5 bottom) and 10 with the flanker in front (5 up and 5 bottom)). In this condition, the flanker may influence stereovision perception either when it is located in front or after the target peg.(iv) Only target condition: 20 trials with only the target inserted in the same locations as in the ‘no depth difference’ condition. This is the control condition to investigate the potential effect of the flanker on the position of the target.

A custom python script has been developed to show the experimenter where to insert the pegs for each trial, randomizing the order. The possible configurations can be seen in Fig. 1. The participant is instructed to open the eyes when they hear a ‘beep’ (when they see the peg configuration) and close them again once the peg is inserted in the cylinder.

**Fig. 1 Fig1:**
[figure not shown]
Possible configurations of the pegs used in the reaching and grasping at different depths task

To record the participant’s motion, we will use reflective markers attached to the tip of the index and thumb, on the head of the 3^rd^ metacarpophalangeal joint. An additional marker will be placed at the nasion, to monitor head motion. Lastly, a marker will be placed at each tip of the pegs. Participant’s motion will be recorded with a V120:Trio camera (OptiTrack NaturalPoint, USA).

We will split it into reaching phase, manipulating phase and withdrawal phase. From each phase, we will extract movement duration, reaction time, smoothness, maximum grip aperture and time to maximum grip aperture [47–50]. To evaluate the movement duration, we will calculate the time passed from the start to the end of the movement. To evaluate the reaction time, we will calculate the time passed from the start of the trial (indicated with a custom script) to the start of the movement. To evaluate the smoothness, we will extract the information from the marker placed on the hand and we will calculate its trajectory straightness. The straighter, the smoother the data are, which indicates better motor control. To evaluate the maximum grip aperture, we will extract the difference between the positions of the marker on the index and the marker on the thumb. The maximum difference will be used. To evaluate the time to maximum grip aperture, we will extract the difference between the positions of the marker on the index and the marker on the thumb. The time at which the maximum difference occurred will be used. This will be done for three conditions: monocular dominant, monocular non-dominant, and binocular.

##### Quality of life

Eye-related quality of life and functional vision in people with visual impairment will be assessed with the PedEyeQ questionnaire [13, 51], including one for the parents of participants younger than 14 years old and an adapted version for participants older than 18 years old. This questionnaire will not be completed by healthy individuals or their parents.

Rasch scores for each questionnaire item will be obtained from published look-up tables available at www.pedig.net, and used to calculate a score for each participant (Parent-PedEyeQ for < 18-year-olds; adapted Child-PedEyeQ for > 18-year-olds). Scores will also be converted to a 0–100 scale to aid in interpretation. The Child PedEyeQ version includes the fields Functional Vision, Bothered by Eyes and Vision, Social, Frustration / Worry. The Parent PedEyeQ version includes the fields Impact on Parent and Family, Worry about Child’s Eye Condition, Worry about Self-perception and Interactions, Worry about Functional Vision. These tests are measured at every assessment point.

#### Secondary outcomes III: Brain activity

We will use a 128-channel eWave + cap connected to an amplifier (ScienceBeam, Shenzen, China) to record continuous EEG during the selective attention and motor control tasks (1000 Hz sampling rate). Electrode impedances will be kept below 50 kΩ, and electrodes will be referenced to the Cz electrode. Offline filtering will involve a 0.1 Hz high-pass, 40 Hz low-pass, as well as a 50 Hz notch using a second-order Butterworth filter (–12 dB/octave roll-off, computed linearly with forward and backward passes to eliminate phase-shift). EEG will be next screened for transient noise, eye movements, and muscle artefacts using an automatic artefact rejection criterion of ± 100 μV for adults and ± 150 μV for children, along with visual inspection. Data from artefact contaminated electrodes across all groups will be interpolated using three-dimensional splines [52].

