##### Oscillatory analyses: Motor control data

For this study, we are especially interested in the primary motor and visual cortices bilaterally. The communication between these two distant brain areas provides the basis for integration of complex information, that helps us adapt our movement to changes in the environment [54]. Besides these two main areas, visuomotor tasks involve the supplementary motor area, the primary sensory cortex, the premotor cortex and the parietal cortex [55, 56]. Given the number of involved areas, we will include all electrodes in the oscillatory analysis. Once the data are cleaned according to the abovementioned procedures, we will divide the data according to each movement segment (reach, manipulate, withdraw). An additional segment of interest is the pre-movement segment, that corresponds to 2000 ms before the GO signal and 1000 ms after (to include the first part of motion) [57]. The EEG and behavioral data will be synchronized post-hoc using timestamps.

We will perform time–frequency analysis to investigate the power at a specific frequency band during the different segments (or epochs) of the task execution (see below). Time–frequency analysis can characterize the temporal dynamics of three of the features of oscillations contained in the EEG data: frequency, power, and phase [58]. Time–frequency power and the phase synchrony will be computed. Time–frequency power has been used to link brain activity to a variety of cognitive and motor mechanisms. Phase synchrony provides information about the timing of the oscillations at a specific frequency and can be examined across trials to capture how consistent or synchronous the phase of the oscillations is across trials [58]. Additionally, this technique provides a close interpretation of the neurophysiological mechanisms. Time–frequency analysis measures the dynamic changes in amplitude and phase of neural oscillations across different frequencies [58]. In a recent study, time–frequency analysis has been shown to be able to depict increased connectivity between the visual and motor cortex during action observation, compared to connectivity between other brain areas, whilst other techniques did not detect such pattern [59].

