In this investigation, we will explore the changes in alpha, beta, and gamma frequencies. Whilst alpha power seems to predict accuracy in visuomotor tracking tasks [55], changes in beta frequency are related to movement planning and execution [60]. Increased synchronization in the high gamma-frequency range has also been shown to be related to active movement initiation [61], which may provide additional insights on the cortical dynamics of motor control.

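### The 40 Hz low-pass carried into the motor-control EEG analysis is inconsistent with the planned gamma analysis and its high-gamma rationale.

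*Protocol article*

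**What the plan says.** Under Secondary outcomes III: Brain activity, the protocol will "record continuous EEG during the selective attention and motor control tasks (1000 Hz sampling rate"), so one paragraph covers both tasks. It continues: "Offline filtering will involve a 0.1 Hz high-pass, 40 Hz low-pass, as well as a 50 Hz notch using a second-order Butterworth filter", with a "12 dB/octave roll-off" and "computed linearly with forward and backward passes to eliminate phase-shift". Artefact handling comes after the filter: "EEG will be next screened for transient noise, eye movements, and muscle artefacts".

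Under Oscillatory analyses: Motor control data, the data are segmented "Once the data are cleaned according to the abovementioned procedures". Time–frequency power and phase synchrony are then computed. On bands, the section says "we will explore the changes in alpha, beta, and gamma frequencies". The only reason given for gamma is this: "Increased synchronization in the high gamma-frequency range has also been shown to be related to active movement initiation".

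No separate filter is given for the oscillatory analysis, and no frequency limits are given for gamma or high gamma.

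**The concern.** A low-pass at 40 Hz suits evoked potentials. It is in the wrong place for an analysis that looks above 40 Hz, and the protocol's reason for including gamma lies in the high-gamma range. Followed as written, the plan suppresses most of the activity it sets out to study and then reports on it under the name gamma.

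Two misreadings would follow. A change in gamma power could be taken as evidence on high gamma when it mostly describes the edge of the band next to beta. A null result could be taken as absence of high-gamma change when the preprocessing had weakened the estimate. Cortical responses during motor control belong to aim (f). Electrophysiological changes in motor control also enter the structural equation model that serves aim (h), although the protocol does not name gamma as a predictor there.

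**Working it through.** **Inputs.** From the brain-activity section: low-pass 40 Hz, second-order Butterworth, −12 dB/octave, forward and backward passes, sampling at 1000 Hz. Assumptions, because the protocol gives no limits: gamma starts at 30 Hz and ends at 80 or 100 Hz; high gamma starts at 60 Hz or above. I take 40 Hz as the half-power point of each pass.

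**Formula.** With r = tan(πf/1000) / tan(π·40/1000), one pass of order n retains a power fraction 1/(1 + r^(2n)). Two passes retain the square of that.

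**The plan's own figure.** One second-order pass has amplitude gain 0.402 at 60 Hz and 0.101 at 120 Hz. 20·log10(0.101/0.402) = −12.0 dB over that octave, so the stated roll-off is reproduced if it describes a single pass.

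**Power retained.** Worked example at 60 Hz: r = 1.510 and r⁴ = 5.20; one pass retains 1/6.20 = 0.161; two passes retain 0.161² = 0.026. The last column covers the other reading, in which −12 dB/octave is the net slope of two first-order passes: r² = 2.28, and (1/3.28)² = 0.093.

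| Frequency | Two second-order passes | Two first-order passes |
|---|---|---|
| 20 Hz | 89% | 64% |
| 30 Hz | 58% | 41% |
| 40 Hz | 25% | 25% |
| 50 Hz (before notch) | 8.3% | 15% |
| 60 Hz | 2.6% | 9.3% |
| 80 Hz | 0.3% | 3.8% |
| 100 Hz | 0.05% | 1.7% |

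At 50 Hz the notch then takes out what is left.

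**If the cut-off is corrected for two passes.** Some software sets each pass so that 40 Hz is the half-power point after both. Then (1 + c)² = 2 gives c = 0.414, and the retained fraction is 1/(1 + 0.414·r⁴)². At 60, 80 and 100 Hz, r⁴ is 5.20, 17.06 and 43.8, which gives 10%, 1.5% and 0.3%.

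**What a band average would then describe.** For a flat spectrum, two second-order passes retain on average 40.4% over 30–40 Hz and 12.56% over 30–80 Hz. The share of remaining 30–80 Hz power that comes from 30–40 Hz is (0.404 × 10)/(0.1256 × 50) = 4.04/6.28 = 64%, against 10/50 = 20% before filtering. With two first-order passes it is (0.3245 × 10)/(0.1524 × 50) = 43%. If power falls as 1/f², the 30–40 Hz share is (1/30 − 1/40)/(1/30 − 1/80) = 40% before filtering. After it, with weighted averages of 0.4204 and 0.2171, the share is 0.40 × 0.4204/0.2171 = 77%; for two first-order passes it is 0.40 × 0.3322/0.2131 = 62%.

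**The case against.** **All gamma is lost.** A reader might infer this. The figures do not support it: the roll-off is gradual, and 30–40 Hz keeps roughly a third to two fifths of its power. The planned outcome is gamma without limits, and high gamma appears only in the rationale.

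**What remains is filter residue or amplifier noise.** A reader might infer this too, and it is too strong. The filter is linear, zero-phase and applied offline, so at any one frequency it scales brain signal and recorded noise by the same factor. Relative power change and phase consistency at that frequency are not destroyed by the scaling. In a simulation with assumed 1/f plus white noise, 80 trials and 7-cycle wavelets, the relative power change from an added burst fell from 1.18 to 1.09 dB at 35 Hz, from 2.16 to 1.54 dB at 80 Hz and from 2.65 to 1.59 dB at 100 Hz. Phase consistency at 80 Hz fell from 0.37 to 0.31. Without a burst, no spurious effect appeared. The loss is therefore dilution, through leakage from the better-preserved lower frequencies, together with the gap at the notch. Retained power is not the same thing as retained information.

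**Cleaning may mean only artefact rejection and interpolation.** This is possible, and a fuller handbook exists. But filtering stands first in the paragraph, artefact screening follows on filtered data, the back-reference is unrestricted, and no other filter is named. If a different pipeline is intended, the current text misstates it and still needs correcting.

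**The analysis is exploratory.** This stands, and it limits how much the point matters.

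**Conclusion.** The filter and the gamma analysis are inconsistent in the current text. With two second-order passes, power at 60 Hz and above falls to 2.6% or less. With two first-order passes it falls to 9.3% or less, and with a cut-off corrected for two passes to about 10% or less. At 80 Hz and above, each of these readings removes at least 96%. Low gamma, about 30–40 Hz, is attenuated but usable.

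Band-level gamma power would be shifted strongly towards the 30–40 Hz edge: from 20% to between 43% and 64% of 30–80 Hz power for a flat spectrum, and from 40% to between 62% and 77% for a 1/f² spectrum. High-gamma estimates would be diluted, so a null result there would not show that high gamma is unchanged.

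This rests on the assumed band limits and on the natural reading that the oscillatory analysis starts from the filtered data. It should be corrected, but it concerns one of three bands in an exploratory secondary outcome. It does not touch best corrected visual acuity or the sample size.

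**What to change.** State in the brain-activity section that the 40 Hz low-pass applies to the evoked-potential analyses (ERP and VEP) only, and state the gamma limits in Hz. Then choose one of two routes before the data are analysed:

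- **Keep high gamma.** Re-filter the stored 1000 Hz raw motor-task recordings with a low-pass above the top of the stated band, and with notches at 50 Hz and at any line harmonic inside the band. Report power by frequency or in narrow sub-bands, so that 30–40 Hz does not stand in for the rest.
- **Drop it.** Limit the oscillatory outcomes to alpha and beta, or to gamma below 40 Hz with the attenuation acknowledged, and remove the high-gamma rationale.

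The first route costs a second preprocessing run and stricter muscle-artefact rejection, because the wider band admits more muscle activity. The second costs only a change of text. Neither needs new participants, visits or recordings.

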##### Event-related potential analyses

For event-related potential (ERP) analyses, after data cleaning, the EEG will be segmented into peri-stimulus epochs from 100 ms before stimulus onset to 500 ms after the stimulus onset. Subsequently, epochs will be averaged according to the relevant conditions, and baseline corrected. The sensory and attentional processes measured with ERPs will be analyzed with traditional analyses of ERP correlates of those mental processes (see below), followed by multivariate analysis of EEG activity elicited in the well-known time-windows of the said ERP correlates. Multivariate analyses of the EEG/ERPs focus on the reference-independent characteristics of the whole electrical field across the scalp. Here, the multivariate analyses will focus on two different measures. First, we will analyze if potential differences in EEG/ERPs across conditions and/or populations stem from modulations in the topographic EEG activity. Differences in the topography of EEG response forcibly indicate that different configurations of sources have been recruited during responses across conditions/populations of interest. The topographic analyses here will involve clustering of the group-averaged EEG/ERP activity over the time-window of the ERP components of interest. These analyses are aimed at identifying periods of stable topographic patterns (topographic maps) and differences therein across conditions of interest. After the selection of an optimal number of topographic patterns explaining the EEG data, the patterns are fit back onto single-subject data; parameters like the EEG pattern duration (or map onset, map offset) and global explained variance will be analyzed. Second, we will analyze, if the potential differences in the EEG/ERPs stem from modulations in the strength of brain responses across different conditions/populations. Global Field Power (GFP) is the standard deviation of the moment-by-moment voltage of the electrical field across the whole scalp and reflects differences in the strength of brain response, across two or more conditions, within a statistically indistinguishable brain network.

These outcomes will be measured at every time point and the assessors will not be masked to treatment allocation, as these are objective measures.

##### Cortical visual responses

Visual evoked potentials (VEPs) will be extracted from the continuous EEG measures to assay the time-locked response to the visual targets and by extension the integrity of the cortical visual processing pathway. VEPs are informative about the spatio-temporal brain dynamics of sensory and perceptual processes. They consist of a sequence of voltage peaks measured over the occipital electrodes: negative peak (N100), positive peak (P100), followed by a negative peak (N200). VEPs will be recorded, for each eye separately, from responses to the color targets in the selective attention task [53]. These target-elicited VEPs are large in both children (+ 4 years old) and adults, and as such should serve as robust EEG markers of the visual cortical pathway integrity related to the fellow/dominant and amblyopic/non-dominant eye in adults and children.

Integrity of the sensory visual processes will be measured by differences in 1) the sequence and/or duration of EEG patterns and 2) the strength of brain response, measured with GFP, elicited by the visual targets over the VEPs’ time-window across different eye conditions and populations.

##### Selective attention processes

Typically, EEG/ERP processes underlying selective attention are measured with the N2pc component, a traditional marker of attentional selection of target objects among distractors. The N2pc is a negative-going voltage deflection observed approx. 200–300 ms after presentation of the stimulus of interest, larger over electrodes contralateral than ipsilateral to the side of the stimulus. The strength of visual selective attention here will be measured by the difference in the mean amplitude of the N2pc elicited by distractors that matched vs. mismatched the color of the target. Respectively, the strength of audiovisual selective attention here will be measured by comparing the N2pc mean amplitude across distractors presented alone vs. with sound.

For multivariate analyses, the strength of different types of selective attention here will be measured by the difference in the duration of EEG patterns present over the N2pc time-window elicited by distractors that match vs. mismatch the target color (visual selective attention), and distractors presented alone vs. with sound (audiovisual selective attention), in line with our previous studies on the development of neurocognitive processes underlying audio-visual attention in healthy populations [32, 46, 53]. In turn, for the GFP analyses, strength of visual and audiovisual selective attention here will be measured by the difference in the GFP elicited over the N2pc time-window by distractors that match vs. mismatch the target color (visual selective attention), and distractors presented alone vs. with sound (audiovisual selective attention).

